### **11.3 Sample size and power determination**

The primary endpoint of saturated fat intake reduction will be assessed by calculating the proportion of subjects who reduced that intake within each of the four treatment groups and comparing these proportions. Comparisons between groups will then be based on 100 subjects per group. Comparisons between the factors (i.e. 'use of the Heart-Age tool' and 'use of planning') will be based on 200 subjects.

A sample size of 200 subjects per cell will allow a difference in proportions of correct responses of approximately 0.08 to be detected at a two-sided 0.05 significance level with power of 0.8, assuming that the lower proportion is around 10% of subjects (i.e. the 10% of non-Heart-Age users their saturated fat intake, then we would need 18% of Heart-Age users to reduce to have a good chance of detecting a significant difference).

A sample size of 100 subjects per cell will allow a difference in proportions of correct responses of approximately 0.12 to be detected at a two-sided 0.05 significance level with power of 0.8, assuming that the lower proportion is around 10% of subjects (i.e. the 10% of Heart-Age non-planners reduce their saturated fat intake, then we would need 22% of Heart-Age planners to reduce to have a good chance of detecting a significant difference).

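### At the stated 10% base rate, the detectable differences of 0.08 (200 per group) and 0.12 (100 per group) have about 64% power, not the 80% claimed in section 11.3.

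*Protocol*

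**What the plan says.** Section 11.3 defines two kinds of comparison of the proportion of subjects who reduced their saturated fat intake. For single conditions, "Comparisons between groups will then be based on 100 subjects per group". For the two design factors (Heart-Age use, planning), comparisons "will be based on 200 subjects". Section 4.1 agrees: it plans 400 participants at Time 3, 100 in each cell of the 2x2 design and so 200 at each level of a factor.

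Two power statements follow:

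- Factor comparison: "A sample size of 200 subjects per cell will allow a difference in proportions of correct responses of approximately 0.08 to be detected". The worked example takes 10% in non-users, and "then we would need 18% of Heart-Age users to reduce to have a good chance of detecting a significant difference".
- Cell comparison: "A sample size of 100 subjects per cell will allow a difference in proportions of correct responses of approximately 0.12 to be detected". The worked example takes 10% in Heart-Age non-planners, and "then we would need 22% of Heart-Age planners to reduce to have a good chance of detecting a significant difference".

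Both carry the same conditions: "to be detected at a two-sided 0.05 significance level with power of 0.8, assuming that the lower proportion is around 10% of subjects". Section 11.2 confirms that design-factor comparisons are reported two-sided.

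**The concern.** Every input to the two power statements is printed beside them, so they can be checked directly, and they do not reproduce. This is the protocol's only sample-size justification, and it concerns the primary endpoint in the form in which it is to be analysed. If the claim is wrong, ethics reviewers and later readers are told that the trial has an 80% chance of detecting 8-point and 12-point effects when its chance is materially lower. A non-significant result could then be given more weight against effects of that size than the design supports.

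There is also a labelling slip. The first statement attaches 200 subjects to a cell, but a cell holds 100; 200 is the number at each level of a factor.

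**Working it through.** **Inputs** (section 11.3): two-sided alpha 0.05, so z = 1.960; power 0.80, so z = 0.8416; lower proportion p1 = 0.10; equal groups. Section 4.1 gives 100 per cell and 200 per factor level as Time 3 numbers, so no further deduction for drop-out is made.

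**Formulas** (pooled variance under the null), with d = p2 − p1, m = (p1 + p2)/2, A = √[2m(1 − m)] and B = √[p1(1 − p1) + p2(1 − p2)]:

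- n per group = [1.960·A + 0.8416·B]² / d²
- power = Φ{(d·√n − 1.960·A) / B}

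**1. The plan's claim for 200 per group, 10% v 18%.** m = 0.14, A = √0.2408 = 0.4907, B = √(0.0900 + 0.1476) = 0.4874.

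- n = (0.9618 + 0.4102)² / 0.0064 = 294.1, so 295 per group.
- Power at 200 = Φ[(0.08 × 14.142 − 0.9618) / 0.4874] = Φ(0.348) = **63.6%**.

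**2. The plan's claim for 100 per group, 10% v 22%.** m = 0.16, A = √0.2688 = 0.5185, B = √(0.0900 + 0.1716) = 0.5115.

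- n = (1.0162 + 0.4305)² / 0.0144 = 145.3, so 146 per group.
- Power at 100 = Φ[(0.12 × 10 − 1.0162) / 0.5115] = Φ(0.359) = **64.0%**.

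**3. Differences that do reach 80% from a 10% base.** Solving for p2 gives 0.0997 with 200 per group and 0.1496 with 100 per group. In reverse, the formula gives n = 199.0 for 10% v 20% and n = 99.5 for 10% v 25%, so these fit the planned sizes almost exactly. Relative to the stated values: 0.0997/0.08 = 1.25 and 0.1496/0.12 = 1.25.

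**4. Does another method rescue the claim?**

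| Method | 10% v 18%, 200 per group | 10% v 22%, 100 per group |
|---|---|---|
| Pooled normal | 63.6% | 64.0% |
| Unpooled normal | 64.1% | 65.0% |
| Arcsine | 64.4% | 65.3% |
| Chi-square, exact enumeration | 64.3% | 65.3% |
| Continuity-corrected | 58.0% | 56.5% |
| Fisher's exact test | 58.7% | 58.3% |
| Pooled normal, one-sided 0.05 | 74.7% | 75.1% |

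**5. Does looser reading of the inputs rescue it?**

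- *Rounding of the difference.* The largest values that still round to those stated, 0.0849 and 0.1249, give 68% and 67%.
- *Base rate.* With 200 per group, power for a difference of 0.08 is 69.3% at an 8% base, 76.2% at 6% and 80.1% at 5%. With 100 per group, power for 0.12 is 68.9% at 8%, 77.8% at 5% and 81.2% at 4%. Reaching 80% needs a base rate of half the stated value or less.

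**The case against.** The best defence does not dispute the arithmetic; it limits what should be drawn from it.

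- **Cause of the error.** A 5% base rate would give detectable differences of 0.080 and 0.124, which suggests that the wrong base rate was used. But applying the 10% variance to both groups, 2.80 × √(2 × 0.1 × 0.9/n), gives 0.084 and 0.119, which round to the stated figures equally well. The document does not settle which, if either, occurred. This objection stands: the origin is unknown, and the finding does not depend on it.
- **The cell label.** The preceding sentence of section 11.3, and section 4.1, make it clear that 200 is a factor-level number, so few readers would be misled. This stands as to weight: it is a minor wording correction.
- **Reading of a null result.** What a null result excludes depends on the observed confidence interval, not on planning power, and the protocol does not say that it will be read otherwise. This stands too; the firm consequence is the misstated power itself.
- **Scope of the 64%.** It applies to an unadjusted comparison of two proportions at exactly the target numbers. Section 11.2 plans a logistic model with interaction, stratification variables and covariates, and section 4.1 allows for more than 400 completers. That is a fair condition on the figure. However, the protocol's own claim is framed as the same simple comparison at the same numbers, so it is the right basis for checking it.
- **Wording such as approximately and around.** This does not help: step 5 shows that the latitude required is far larger than those words allow, and the worked examples fix 10%, 18% and 22%.
- **A later analysis plan.** It could not make a power statement printed in the protocol true.

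**Conclusion.** The concern holds. Under the inputs in section 11.3, power is about 64% for both stated differences (63.6% and 64.0% by the pooled formula, 64–65% by the other uncorrected two-sided methods, 57–59% with continuity correction or Fisher's exact test), against 80% claimed. Effects of the stated size would be missed about 36% of the time rather than 20%. The differences detectable with 80% power are 0.10 and 0.15.

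This rests on a 10% lower proportion, a two-sided 0.05 level, an unadjusted comparison, and 200 per factor level or 100 per cell with data at Time 3. It says nothing about the interaction test, for which power would be lower.

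**What to change.** In section 11.3:

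1. For the factor comparisons (200 v 200), replace 0.08 by 0.10 and 18% by 20%.
2. For the cell comparisons (100 v 100), replace 0.12 by 0.15 and 22% by 25%.
3. Describe the 200 as per factor level, not per cell.

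As an alternative to items 1 and 2, keep 0.08 and 0.12 and state power of about 64% for each. Either way the change is to protocol wording only, with no extra subjects; the cost is that the stated sensitivity becomes less favourable.

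If the sponsor wants 80% power for the differences now printed, that is a change of design. It needs 295 per factor level (2 × 295 = 590 completers), which also covers 146 per cell (4 × 146 = 584), in place of 400. At the ratio in section 6.2 of 900 recruited for 400 completing, that means about 590 × 900/400 ≈ 1,330 recruits, and the cap of 900 in the Appendix 6 invitation would have to change.

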## 2. Study Objectives

### 2.1 Primary Objectives

#### Objectives:

The primary aim of the present study is to test the effects of the Heart-Age and Planning on Motivation to Change and Saturated Fat Intake over a period of two weeks. It is hypothesised that Heart-Age will exert its effect on motivation and planning on behaviour and that in combination they would fare better than if used independently.

To assess the above, two questionnaires will be issued:

1. Margetts et al (1989) self-report index of food
2. A two item self-perception of saturated fat intake to account for any reporting and demand characteristic biases

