## 4. Study Population

### 4.1 Total Number and Nature of Subjects

We will over-recruit at Time 1 to be able to take into account any drop-outs likely to occur over the study period. The aim will be to end up with 400 (or more) participants at Time 3. 100 subjects will be used for each cell of a 2x2 factorial design with the factors 'use of the Heart-Age tool' and 'use of planning'. Thus 200 subjects will use the Heart-Age site, 100 of these will plan how to reduce their saturated fat intake and the other 100 will not. Of the remaining 200 subjects, 100 will also be asked to plan how to reduce their saturated fat intake. The final 100 will act as a Control group (neither using the Heart-Age tool nor planning how to reduce their saturated fat intake).

Subjects will be recruited from both genders, be 30-60 years old and will have a high level of at least one risk factor for CHD (normally obesity). This inclusion of subjects with at least one risk factor has been deliberate. It is believed that these subjects,

though at no immediate risk of developing heart disease, will be more likely to benefit from presentation of information on their heart-health. If the information is motivating enough then they will hopefully decide to take some action to maintain or improve their future heart-health. Obese and overweight people are also expected to take into consideration their weight when making health-related judgements. Thus they should consider themselves as being at higher risk than people of average weight (Renner et al, 2000).

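### Section 11.3 claims 80% power for two differences that the planned numbers detect with about 64% power, and its two illustrations do not fit one set of 2x2 cell rates

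*Protocol*

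**What the plan says.** Protocol section 11.3 gives two sizing statements, both with a "two-sided 0.05 significance level with power of 0.8" and a lower proportion of around 10%.

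- Factor comparison: "A sample size of 200 subjects per cell will allow a difference in proportions of correct responses of approximately 0.08". The illustration is that if "the 10% of non-Heart-Age users their saturated fat intake, then we would need 18% of Heart-Age users to reduce", the difference has a good chance of being detected.
- Group comparison: "A sample size of 100 subjects per cell will allow a difference in proportions of correct responses of approximately 0.12". The illustration is that if "the 10% of Heart-Age non-planners reduce their saturated fat intake, then we would need 22% of Heart-Age planners to reduce", the same applies.

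Section 4.1 fixes who is in each comparator. The design is a 2x2 factorial with 100 subjects per cell. The 200 Heart-Age users are 100 planners and 100 non-planners. On the other side, "Of the remaining 200 subjects, 100 will also be asked to plan how to reduce their saturated fat intake", and the last 100 are controls. Section 2.1 adds the hypothesis: "It is hypothesised that Heart-Age will exert its effect on motivation and planning on behaviour", with the combination expected to do better than either alone.

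**The concern.** There are two problems. First, the stated power looks too high for the stated sizes and rates, before any question of design arises.

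Second, the same 10% is given to two differently composed groups. Half of the non-Heart-Age users in the factor comparison are asked to plan. All of the Heart-Age non-planners in the group comparison receive Heart-Age. No rate is given for the control cell, the only one with neither intervention. A reader therefore cannot tell which cell rates the sizing assumes, or what power either comparison has when the other factor also works.

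At stake is how a null result would be read. A trial believed to have 80% power for these differences, but with about 64%, misses a true effect of that size roughly 36% of the time rather than 20%.

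**Working it through.** **Inputs.** From section 11.3: two-sided alpha 0.05; 200 per factor level with 10% v 18%; 100 per cell with 10% v 22%; stated power 0.80 for each. From section 4.1: each factor level is two cells of 100. Section 6.2 recruits 900 to end with 400, so drop-out is already allowed for and 400 is the right basis.

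**Formula.** Two-proportion z-test with n per group, d = p2 − p1 and pbar = (p1 + p2)/2:

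- s0 = √[2·pbar(1 − pbar)/n]
- s1 = √{[p1(1 − p1) + p2(1 − p2)]/n}
- power = Φ[(d − 1.96·s0)/s1]

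**Step 1: the plan's own figures.**

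- 10% v 18%, n = 200: pbar = 0.14, s0 = 0.0347, s1 = 0.0345. Power = Φ[(0.08 − 0.0680)/0.0345] = Φ(0.348) = 0.636.
- 10% v 22%, n = 100: pbar = 0.16, s0 = 0.0519, s1 = 0.0512. Power = Φ[(0.12 − 0.1016)/0.0512] = Φ(0.359) = 0.640.

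Other versions of the test do not recover 0.80:

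| Method | 10% v 18%, n = 200 | 10% v 22%, n = 100 |
|---|---|---|
| Pooled null variance | 0.636 | 0.640 |
| Unpooled variance | 0.641 | 0.650 |
| Arcsine | 0.644 | 0.653 |
| One-sided 0.05 | 0.747 | 0.751 |
| Size per group for 80% power, two-sided | 295 | 146 |

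Solving for the difference with 80% power at a 10% lower rate gives 0.0997 with 200 per group and 0.1496 with 100 per group, that is about 0.10 and 0.15. The protocol states 0.08 and 0.12.

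**Step 2: do the two illustrations share one set of cell rates?** The second puts Heart-Age non-planners at 10% and Heart-Age planners at 22%. These two equal cells are the whole Heart-Age level, so Heart-Age users pool to (10 + 22)/2 = 16%. The first illustration needs 18%, which would require planners at 2 × 18 − 10 = 26%. Keeping the first illustration's 10% for non-Heart-Age users, the factor contrast becomes 10% v 16% at n = 200: pbar = 0.13, s0 = 0.0336, s1 = 0.0335, power = Φ(−0.177) = 0.430. This step needs only averaging, with no assumption about additivity.

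**Step 3: how much does the missing control rate matter?** Assume, for illustration only, that Heart-Age adds 8 points and planning 12, additively, over a control rate c. Non-Heart-Age users are then at c + 6 and Heart-Age users at c + 14. Heart-Age non-planners are at c + 8 and Heart-Age planners at c + 20 (all in percentage points).

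| Control rate c | Factor comparison, n = 200 | Power | Group comparison, n = 100 | Power |
|---|---|---|---|---|
| 0% | 6% v 14% | 0.762 | 8% v 20% | 0.689 |
| 2% | 8% v 16% | 0.693 | 10% v 22% | 0.640 |
| 4% | 10% v 18% | 0.636 | 12% v 24% | 0.599 |
| 6% | 12% v 20% | 0.588 | 14% v 26% | 0.565 |
| 8% | 14% v 22% | 0.549 | 16% v 28% | 0.536 |
| 10% | 16% v 24% | 0.516 | 18% v 30% | 0.511 |

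Under additivity the first illustration corresponds to a control rate of 4% and the second to 2%, so no single control rate yields both.

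**The case against.** The strongest reply is that section 11.3 offers two separate, rounded illustrations of what 200 and 100 per group could detect. It does not forecast four cell rates, and nothing says that the two must hold together. That is fair, and it limits the second part of the point. The two 10% rates can even coexist: with control 4%, Planning 16% and Heart-Age alone 10%, both comparators are at 10%. The mismatch of 16% against 18% comes from the upper rates, not from the shared 10%.

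A reader might go further and infer that the 10% sits on the wrong comparator and belongs to the control arm, so that power is overstated by another 12 to 13 points (52% and 51% instead of 64%). The documents do not support this. That result needs a 10% control rate and additive effects of 8 and 12 points. The protocol states no control rate and no additivity, and it gives 0.08 and 0.12 as detectable differences, not expected effects. Against the step 1 values, the change in power runs from +13 to −12 points (factor comparison) and from +5 to −13 points (group comparison) as the control rate goes from 0% to 10%. The hypothesis in section 2.1, which has Heart-Age acting on motivation and planning on behaviour, also leaves room for Heart-Age non-planners to stay near the untreated rate.

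Section 11.2 plans a logistic model with both factors and their interaction, so a two-proportion test only approximates the planned analysis. But section 11.3 words its claim as a comparison of proportions, and a simulation of the interaction model with cells at 10%, 10%, 18% and 18% gave 63% on the logit scale, close to the 64% here.

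None of these replies touches step 1, which uses only the protocol's own inputs.

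**Conclusion.** The point holds in three parts of unequal strength.

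- **Firm:** the stated 0.80 is about 0.64 for both comparisons, a shortfall of about 16 points. This rests only on the rates, sizes and significance level in section 11.3.
- **Firm but smaller:** the two illustrations cannot describe the same trial, because the second implies 16% for Heart-Age users where the first uses 18%. As separate approximations they need not agree, but both justify the same 400 subjects. Taken together they leave about 43% power for the Heart-Age comparison.
- **Conditional:** with no control-cell rate, the effect of the other factor on power is not determined. With additive effects of 8 and 12 points and a control rate between 0% and 10%, power lies between about 76% and 52% (factor comparison) and between about 69% and 51% (group comparison). It is below 80% throughout that range, but no single value in it is the trial's power.

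**What to change.** In section 11.3:

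1. Restate power as about 64% for differences of 0.08 (200 per level) and 0.12 (100 per cell) at a 10% lower rate. Alternatively, keep 80% power and state detectable differences of about 0.10 and 0.15.
2. State one coherent set of four assumed cell rates, chosen and justified by the sponsor. Derive the non-Heart-Age, Heart-Age and Heart-Age non-planner rates from it.
3. Show power over a range of control rates, saying how the two effects are assumed to combine. Do not enter 52% and 51% as the trial's power, since they rest on a control rate that the protocol does not give.

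This changes wording and figures in one section. Enrolment, design and analysis stay as they are. The cost is a less favourable stated power.

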### **11.4 Definition of Data and Analysis Population**

Data will be recorded by subjects, captured via the on-line system and will be held in compliance with the UK Data Protection Act. Each subject will be identified by a unique ID number assigned to them

The original data will be stored in the computer (but no hard-copies will be kept since this is an online study) and will be filed at Unilever for a minimum of five years from completion of the study.

### **11.5 Responsibilities for Statistical Analysis**

All statistical analyses will be performed by the Unilever Statistics Group, Colworth Park

### **11.6 Reporting of deviations of statistical plan**

Any deviations of the statistical plan will be reported in the analysis.

### **Part III: General Considerations for Conducting a Protocol**

#### **1. Ethical Considerations**

##### **1.1 Declaration of Helsinki**

The current revision of the Declaration of Helsinki is the accepted basis for clinical study ethics, and must be fully followed and respected by all engaged in research on human beings. Any exceptions must be justified and stated in the protocol. Independent assurance that subjects are protected can only be provided by an ethics committee/institutional review board and freely obtained informed consent.

##### **1.2 Good Clinical Practice**

Good clinical practice is a standard for clinical studies, which encompasses the design, conduct, monitoring, termination, audit, analyses, reporting and documentation of the studies. It ensures the studies are ethically justified and scientifically sound, and that the clinical properties of the

diagnostic/therapeutic/prophylactic product under investigation are properly documented. Refer to section 2.1.2 for further guidance.

## **2. Investigators Responsibilities**

It is the responsibility of the investigator(s) to conduct the study according to the protocol and to ensure that (s) he has the subject availability to conduct the study within the period defined in the study protocol.

### **2.1 Ethics**

#### **2.1.1 Declaration of Helsinki**

It is the responsibility of the investigator(s) to ensure that the study is conducted in full conformance with the principles of the current Revised Version (1989) of the Declaration of Helsinki.

#### **2.1.2 Good Clinical Practice**

It is the responsibility of the investigator(s) to ensure that the study is performed in accordance with Unilever's standards for the conduct of Human Trials and according to all local laws and regulations concerning Human studies. It is observed that due to the nature of Unilever human trials these do not qualify as Clinical Trials and as such, are not obliged by law to follow EU Directive 2001/20/EC (Clinical Trials Directive) or EU Directive 2005/28/EC (GCP Directive). However, Unilever Human Trials where possible operate to the spirit of these Directives in order to ensure best practice.

#### **2.1.3 Ethics Committee or Institutional Review Board**

It is the responsibility of the investigator(s) to submit a copy of the protocol and consent form to an ethics committee/institutional review board in order to obtain independent approval to conduct the study. Ethics committee/institutional review board approval must be obtained before the study is started. The approval of the ethics committee/institutional review board must be sent in writing, to the investigator(s). The Ethics Committee approval letter must mention the Ethics Committee members and their function.

#### **2.1.4 Informed Consent**

It is normally the responsibility of the investigator(s) to obtain informed consent from each subject participating in the study, after explanation of the aims, methods, benefits and potential hazards of the study. Since this study is solely conducted online the aims, benefits and potential harms to the subjects will be explained online (Appendix 2). The consent must and will be obtained before any study-specific procedures are performed.

It must be made completely and unambiguously clear to each subject that they are free to refuse to participate in the study, or that they can withdraw their consent at any time and for any reason, without incurring any penalty or withholding of treatment on the part of the investigator.

